#### 2.3.3. Pain Beliefs and Perceptions Inventory

The Pain Beliefs and Perceptions Inventory (PBPI) is a self-report questionnaire designed to identify cognitive and behavioral factors that influence pain management and athletic performance. The PBPI is a widely used, comprehensive, and psychometrically sound instrument that is brief and easy to administer. It consists of 16 items distributed across three subscales: (i) Time, (ii) Mystery, and (iii) Self-Blame [58]. Each item is rated on a 5-point Likert scale ranging from −2 to +2. The total score is calculated after reversing the score (2 → −2) for items 3, 9, 12, and 15, yielding a possible score range from −32 to +32 [59]. Higher total scores indicate more negative beliefs about pain and its management, which are associated with increased levels of anxiety, depression, disability, and pain severity [60]. The Greek version of the PBPI-16 has been validated in the Greek population, demonstrating high internal consistency (Cronbach’s α = 0.89–0.96) and good test–retest reliability (ICC = 0.73–0.82) among individuals with chronic pain [59].

#### 2.3.4. Sympathetic Skin Response: Autonomic Nervous System Function

Autonomic nervous system function will be evaluated through Sympathetic Skin Response (SSR) and through grip strength in two phases: pre-intervention and 4 weeks post–BB intervention for all three groups. Additionally, these procedures will be repeated during the follow-up period.

SSR is a neurophysiological tool designed to assess the functional integrity of the sympathetic cholinergic sudomotor pathways. It is a non-invasive, routine test used to assess autonomic dysfunction, specifically measuring how sweat glands (sudomotor activity) respond to various stimulus, such as electrical or auditory stimulation. SSR testing will be conducted using the Dantec Keypoint system (version 5.13; Alpine Biomed ApS, Skovlunde, Denmark), following the standard protocol [61]. All athletes will be instructed to refrain from smoking and to consume only a light breakfast, excluding alcohol and caffeine. The examination room temperature will be maintained at 23–26 °C, and limb temperature at 32–33 °C. Recordings will be obtained using surface, circular electrodes. The active electrodes will be positioned on the left palm and right sole, while the reference electrodes will be placed on the dorsum of the corresponding hand and foot. Electrical stimuli will be delivered to the right wrist at an intensity of 75 mA and a duration of 0.1 ms. The band-pass filter will be set between 0.5 and 2000 Hz. Five stimuli will be administered unpredictably at random intervals of at least 30 s. Latency will be measured from the onset of the stimulus artifact to the first deflection from baseline (in seconds), and amplitude will be measured peak-to-peak (from negative to positive peak, in millivolts). The shortest latency and the highest amplitude among the five responses will be used for statistical analysis. Parameters included in the analysis will be: SSR upper-limb latency, SSR upper-limb amplitude, SSR lower-limb latency, and SSR lower-limb amplitude (Figure 2, Figure 3 and Figure 4).

#### 2.3.5. K-Force Dynamometer: Hand Grip Strength

Hand Grip Strength Test (HGS) is a widely used method for assessing grip strength through the performance of a maximal voluntary contraction (MVC) [63]. The HGS has demonstrated high test–retest reliability (ICCs = 0.90–0.99) in evaluating grip force during maximal isometric contractions [64]. In the present study, MVC will be recorded using the K-Force Controller (KFC) portable dynamometer (Kinvent Biomécanique SAS, Montpellier, France). Data will be transmitted via Bluetooth Low Energy (2.4 GHz) to the Kinvent software (version 2.24.1; Kinvent Biomécanique SAS, Montpellier, France), where they will be stored and exported to external data storage devices. The K-Force Grip dynamometer has been shown to have excellent reliability (ICC = 0.96–0.97) in recording grip strength [65]. For the test procedure, participants will be seated with the shoulder in a neutral position, the elbow flexed at 90° without support, the forearm in a neutral position, and the wrist positioned between 0° and 30° of dorsiflexion and 0–15° of ulnar deviation. After MVC assessment, participants will be instructed to squeeze the dynamometer handle at an intensity corresponding to at least 30% of their MVC, a threshold known to elicit autonomic nervous system activation. Participants will perform three trials, each lasting 30 s, with 1 min rest intervals between trials. The test will be performed bilaterally, beginning with the dominant upper limb, using identical positioning and testing procedures for both sides.

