## Abstract

**Background/Objectives:** This study aims to evaluate the effectiveness of binaural beats (BB) on the autonomic nervous system (ANS), kinesiophobia of reinjury and fitness biomarkers in professional athletes with chronic musculoskeletal injuries. **Methods**: A total of 54 athletes aged 18–25 years, engaged in open-skill sports and experiencing chronic lower-limb injuries for over three months, will be recruited. They will be randomly assigned to one of three groups: an intervention group, a placebo group, and a control group. All athletes will undergo a 15 min auditory intervention five times per week for four weeks. The intervention group will listen to BB embedded in music at high beta and gamma frequencies (30–100 Hz) with guided instructions. The placebo group will receive placebo BB within the same music framework, while the control group will listen only to the music background. Assessments will be conducted at baseline, immediately post-intervention, and at a 4-week follow-up. The primary outcomes will be kinesiophobia of reinjury, ANS function, and heart rate variability (HRV), assessed using the Tampa Scale of Kinesiophobia (TSK-17), Sympathetic Skin Response (SSR), and HRV analysis, respectively. Secondary outcomes will include sport-related anxiety and pain beliefs, assessed using the Sport Competition Anxiety Test (SCAT-15) and the Pain Beliefs and Perceptions Inventory (PBPI-16), respectively; handgrip strength, assessed using the Hand Grip Test; and fitness-related biomarkers, including maximal oxygen uptake (VO_2_max) and blood lactate concentration. **Conclusions**: These findings may provide evidence supporting BB as a complementary, non-invasive intervention to enhance psychological and physiological rehabilitation in injured athletes. Ethics and Dissemination: The study has received ethical approval and is registered on ClinicalTrials.gov. Findings will be disseminated through peer-reviewed publications, conferences, and academic presentations.

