Kinesiophobia is defined as an excessive, irrational fear of movement or physical activity stemming from a perceived vulnerability to pain or reinjury [18]. Elevated levels of kinesiophobia have been positively associated with anxiety, depressive symptoms, attentional disturbances, and reduced self-efficacy during RTS [19,20]. In athletes following anterior cruciate ligament (ACL) reconstruction, kinesiophobia—alongside pain, anxiety, depression, and low self-esteem—has been shown to impair RTS and increase reinjury likelihood across multiple sports, including football, basketball, handball, and rugby [17,19]. Similarly, chronic ankle instability has been linked to heightened kinesiophobia and diminished functional capacity in athletic populations [21]. The Tampa Scale of Kinesiophobia (TSK) is widely used to quantify fear of movement in injured athletes and has demonstrated strong psychometric properties across sports and clinical contexts [22].

Beyond psychological factors, MSK-has been shown to influence central and peripheral nervous system functioning, particularly the Autonomic Nervous System (ANS). Emotional and cognitive responses to injury can modulate ANS activity, shifting the balance between sympathetic (“fight-or-flight”) and parasympathetic (“rest-and-digest”) responses [23]. Cardiovascular regulation, vasomotor activity, and electrodermal responses represent key physiological pathways through which emotional stress and pain-related cognitions manifest following injury [24]. Heart rate variability (HRV) and sympathetic skin response are widely recognized as sensitive indicators of ANS function and autonomic balance [24]. Studies demonstrated that the Isometric Hand Grip Test (IHG) can be a supplementary test to assess autonomic nervous system regulation through metrics the changes in heart rate and blood pressure during implementation is isometric contraction at 30% MVC [25,26].

Emerging evidence suggests that pain intensity, pain catastrophizing, and perceived disability following injury and chronic pain are closely associated with alterations in HRV, reflecting dysregulation of autonomic control [27,28]. Conversely, findings in elite football players indicate a transient increase in HRV approximately 72 h post-injury, suggesting enhanced parasympathetic activation during early recovery [29]. Despite these insights, the relationship between ANS function and kinesiophobia in injured athletes remains largely unexplored.

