Athletes who participate in open-skill sports were selected because these sports involve unpredictable movement environments, which may increase the risk of lower-limb injury. Therefore, interventions that improve autonomic regulation, such as binaural beats, may help reduce fear of reinjury.

Therefore, based on this theoretical and clinical reasoning, the present study aims to investigate the effects of binaural beat stimulation on kinesiophobia of reinjury, on ANS function through the Sympathetic Skin Response (SSR) and the Isometric Hand Grip test (IHG) and the fitness biomarkers such as VO_2_max, blood lactate concentration, and HRV in professional athletes with chronic lower-limb musculoskeletal injuries (MSK-I). A secondary objective is to examine the maintenance of these effects four weeks after the intervention. It is hypothesized that binaural beats favorably modulate ANS activity, reduce kinesiophobia, reinjury anxiety, and pain beliefs, and enhance aerobic capacity, with sustained effects at follow-up. Conversely, the null hypothesis posits that binaural beat stimulation will not significantly affect ANS function, psychological outcomes, or fitness biomarkers, nor will any effects be maintained after four weeks.

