##### Maximal Oxygen Uptake and Lactate Levels

The ergospirometry test will be conducted on a treadmill following the protocol described by Bielik et al. [66]. Respiratory variables will be recorded using a breath-by-breath gas analyzer (K5, Cosmed, Rome, Italy), calibrated prior to each session according to the manufacturer’s instructions. Maximal oxygen uptake (VO_2_max) will be evaluated as an objective measure of aerobic capacity and as a robust indicator of cardiorespiratory function [67]. VO_2_max will be determined via an incremental graded exercise test (GXT), which progressively increases treadmill velocity until volitional exhaustion, with estimated time of at least 12–20 min [68].

Before the start of the test, the researchers will record HR and blood pressure in a resting state. Athletes will be placed in a supine, relaxed position and instructed to remain still and refrain from speaking for 5 min. Prior to starting the test, all athletes will perform a standardized warm-up comprising 5 min of cycling on a cycle ergometer followed by 5 min of dynamic lower-limb stretching.

The blood lactate concentrations (La) will be measured in two phases before and at the end of the ergospirometry test and the results (mmol) will be used for statistical analysis.

The GXT will begin at 8 km·h^−1^, with velocity increments of 1 km·h^−1^ per minute until volitional exhaustion, maintaining a 0% treadmill gradient. Termination criteria will include (a) a plateau or decline in VO_2_ despite increasing workload, accompanied by a respiratory exchange ratio ≥ 1.10, (b) the ratio VE/VO2 ≥ 30, (c) the ratings of perceived exertion (RPE) 18–20 of borg scale and (d) the concentration of lactic acid in blood ≥ 9 mmol/L [67]. Athletes will receive verbal encouragement, primarily during the final minute. Respiratory variables will be continuously recorded using a breath-by-breath gas analyzer, which will be calibrated prior to each session according to the manufacturer’s instructions. VO_2_ values will be averaged over the final 10 s of each 1 min stage. All procedures will be supervised by two exercise physiologists to ensure participant safety and protocol fidelity. The results of oxygen uptake relative to body mass (VO_2_/kg), the metabolic equivalents (METs) and the ratio of carbon dioxide production to oxygen consumption (VCO_2_/VO_2_), which is defined as respiratory quotient (RQ), will be used for statistical analysis.

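### The hand grip test is presented as a measure of autonomic function, but the only value named for recording is grip force, so the grip part of the autonomic objective cannot be answered as written.

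*Protocol article*

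**What the plan says.** All references are to the protocol article.

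- **Aim (Introduction, last paragraph).** The trial studies effects "on ANS function through the Sympathetic Skin Response (SSR) and the Isometric Hand Grip test (IHG"), among other measures.
- **Rationale (Introduction).** The IHG is described as a supplementary autonomic test. Its readout is "the changes in heart rate and blood pressure during implementation is isometric contraction at 30% MVC". A later paragraph likewise describes the acute autonomic effect of gripping as rises in heart rate, blood pressure and respiratory rate.
- **Section 2.3.4.** "Autonomic nervous system function will be evaluated through Sympathetic Skin Response (SSR) and through grip strength in two phases", with a repeat at follow-up, which makes three visits.
- **Section 2.3.5.** "MVC will be recorded using the K-Force Controller (KFC) portable dynamometer". Athletes are then told to "squeeze the dynamometer handle at an intensity corresponding to at least 30% of their MVC, a threshold known to elicit autonomic nervous system activation". There are three 30 s trials with 1 min rests, on both sides. No response variable is named for these holds.
- **Abstract.** The secondary outcomes include "handgrip strength, assessed using the Hand Grip Test". ANS function is a primary outcome assigned to SSR, and HRV is a further primary outcome.

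**The concern.** The submaximal hold is an autonomic stimulus, and the text says so. A stimulus informs about autonomic function only if an autonomic response to it is read. The force produced during the hold cannot be that response, because the instruction sets it. MVC cannot be either: it reflects strength and effort, and the Introduction itself warns that fear, anxiety or anticipated pain may influence grip performance. The intervention targets fear and anxiety, so a group difference in MVC could arise without any change in autonomic regulation.

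What is at stake is interpretation. Section 2.3.4, read by itself, invites the report to treat a change in grip force as evidence on ANS function. The holds, meanwhile, feed no stated outcome.

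A smaller, related point is that the load has a floor of 30% of MVC and no upper limit. The stimulus can therefore differ between athletes and between visits, which would blur a heart-rate or blood-pressure response even if one were recorded.

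**Working it through.** The plan gives no figure to reproduce on this point, so the check compares passages.

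**Step 1. What would make the grip test autonomic?** By the Introduction, the change in heart rate and blood pressure during contraction at 30% MVC.

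**Step 2. Where are heart rate and blood pressure planned?**

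| Place | Reading | Tied to |
|---|---|---|
| Maximal Oxygen Uptake and Lactate Levels | "Before the start of the test, the researchers will record HR and blood pressure in a resting state" | Treadmill test, at rest |
| Kubios Software: Heart Rate Variability | Heart rate before, during and after exercise | Treadmill test |
| Same section, analysed values | Eight HRV indices, at rest and in three recovery phases | Treadmill test |
| 2.3.5 Hand Grip Strength | None named | n/a |

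Blood pressure appears once as a planned measurement, at rest. No heart-rate or blood-pressure reading is attached to the grip holds.

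**Step 3. What is taken from the grip test?** Section 2.3.5 names MVC. The Abstract lists handgrip strength.

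**Step 4. Compare.** The aim and section 2.3.4 require an autonomic reading from the grip test. Section 2.3.5 and the Abstract supply a strength reading. The variable that would link them is not named anywhere.

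**Step 5. What still measures ANS function?** SSR supplies four parameters (latency and amplitude, upper and lower limb; section 2.3.4). HRV supplies eight indices: RR, HR, SDNN, RMSSD, LF, HF, LF/HF and total power. The gap is therefore limited to the grip test.

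**Step 6. How much testing is affected?** Reading section 2.3.5 as three trials per hand, 3 trials × 2 hands × 3 visits = 18 holds per athlete, or 18 × 54 = 972 if all 54 athletes attend every visit. With the 48 athletes that the sample size section requires before its dropout allowance, the count is 18 × 48 = 864. These are counts of procedures with no stated outcome. They measure neither bias nor loss of power.

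**The case against.** **The article is condensed.** Section 2.3.5 does not say that nothing else is recorded during the holds, and a fuller protocol may specify a heart-rate monitor. A reader might infer that the trial is certain to collect no autonomic reading from the test. The text does not support that much: it is silent on other recordings. The objection does not remove the point, however. Section 2.3.4 positively names grip strength as the ANS measure, against the Introduction's own definition. Section 2.3.5 is also detailed enough to give joint angles, the Bluetooth band and the software version, and the SSR, ergospirometry and HRV sections each list the variables to be analysed.

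**No passage plans to report grip force as an autonomic result.** This stands in large part. The Abstract separates handgrip strength from ANS function. The Discussion says improved ANS function would show in SSR parameters and HRV, and lists handgrip strength among the things that better autonomic regulation may then enhance. A misreading is possible because of the aim and section 2.3.4; it is not a planned analysis.

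**The IHG is only supplementary.** This also stands. A reader might infer that the whole autonomic objective fails, or that the grip result is uninterpretable. Neither follows: SSR and HRV remain, and MVC is interpretable as the strength outcome that the Abstract declares.

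**Conclusion.** The point holds within limits. The aim and section 2.3.4 treat the hand grip test as a measure of ANS function, while the only value named for recording is grip force. As the article is written, the grip component of the autonomic objective cannot be answered, and a change in MVC should not be read as an autonomic effect.

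On the Abstract's outcome list, the primary outcomes (TSK-17, SSR and HRV) are untouched, and so are the sample size and the validity of MVC as a secondary strength outcome. The size of the problem is one supplementary test without an autonomic readout; no numerical bias can be attached to it.

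The conclusion assumes that the article reflects what will be recorded. If a fuller protocol already specifies heart-rate and blood-pressure readings during the holds, what remains is to correct the wording of section 2.3.4 and to name the outcome. The correction is worth making because it is cheap and decides what may be concluded from the grip data.

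**What to change.** Choose one of two options before data are collected or, failing that, before they are reported.

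1. **Remove the autonomic claim.** Delete the IHG from the ANS aim in the Introduction and the reference to grip strength from the opening sentence of section 2.3.4. Keep MVC as a secondary strength outcome and draw no ANS conclusion from grip force. This costs only wording.
2. **Supply the autonomic readout.** In section 2.3.5, record heart rate with the Polar H10 already in use and, where feasible, blood pressure, before and at the end of each hold. Set the hold at one fixed percentage of MVC, used at all visits. Define the IHG autonomic outcome as the change from the pre-hold value, and report MVC separately as strength. The cost is added readings at each visit. Blood pressure is the harder part, since only 1 min separates the holds and the article specifies no blood-pressure device.

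Under either option, the Abstract, the aim and sections 2.3.4 and 2.3.5 should describe the test in the same way.

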#### 2.3.6. Ergospirometry Test: Fitness Biomarkers

An ergospirometry test will be used to evaluate the physical fitness biomarkers such as maximal oxygen uptake (VO_2_max) and blood lactate concentration (REF). All these measurements will be conducted in two phases: pre-intervention and 4 weeks post–BB intervention for all three groups. Additionally, these procedures will be repeated during the follow-up period.

##### Maximal Oxygen Uptake and Lactate Levels

The ergospirometry test will be conducted on a treadmill following the protocol described by Bielik et al. [66]. Respiratory variables will be recorded using a breath-by-breath gas analyzer (K5, Cosmed, Rome, Italy), calibrated prior to each session according to the manufacturer’s instructions. Maximal oxygen uptake (VO_2_max) will be evaluated as an objective measure of aerobic capacity and as a robust indicator of cardiorespiratory function [67]. VO_2_max will be determined via an incremental graded exercise test (GXT), which progressively increases treadmill velocity until volitional exhaustion, with estimated time of at least 12–20 min [68].

Before the start of the test, the researchers will record HR and blood pressure in a resting state. Athletes will be placed in a supine, relaxed position and instructed to remain still and refrain from speaking for 5 min. Prior to starting the test, all athletes will perform a standardized warm-up comprising 5 min of cycling on a cycle ergometer followed by 5 min of dynamic lower-limb stretching.

The blood lactate concentrations (La) will be measured in two phases before and at the end of the ergospirometry test and the results (mmol) will be used for statistical analysis.

The GXT will begin at 8 km·h^−1^, with velocity increments of 1 km·h^−1^ per minute until volitional exhaustion, maintaining a 0% treadmill gradient. Termination criteria will include (a) a plateau or decline in VO_2_ despite increasing workload, accompanied by a respiratory exchange ratio ≥ 1.10, (b) the ratio VE/VO2 ≥ 30, (c) the ratings of perceived exertion (RPE) 18–20 of borg scale and (d) the concentration of lactic acid in blood ≥ 9 mmol/L [67]. Athletes will receive verbal encouragement, primarily during the final minute. Respiratory variables will be continuously recorded using a breath-by-breath gas analyzer, which will be calibrated prior to each session according to the manufacturer’s instructions. VO_2_ values will be averaged over the final 10 s of each 1 min stage. All procedures will be supervised by two exercise physiologists to ensure participant safety and protocol fidelity. The results of oxygen uptake relative to body mass (VO_2_/kg), the metabolic equivalents (METs) and the ratio of carbon dioxide production to oxygen consumption (VCO_2_/VO_2_), which is defined as respiratory quotient (RQ), will be used for statistical analysis.

